## INTRODUCTION

The LAPPRO trial, a prospective, controlled non-randomized trial where robot assisted laparoscopic prostatectomy was compared with open retropubic prostatectomy, is the context for the described study, a secondary outcome of the trial. Inclusion took place during September 2008 until November 2011, with a total of 4003 included patients at 14 Swedish Departments of urology.

Since the middle of 1990s several studies have reported an increased risk for developing an inguinal hernia after prostatectomy [1-6] compared with the normal population. Patients operated with open radical retropubic prostatectomy (RRP) or robot assisted prostatectomy (RALP), had a threefold increased risk of being operated because of inguinal hernia [7]. Hence, evidence suggests an increased incidence of inguinal hernia even after minimal invasive surgery such as RALP[8]. But as some studies suggest the risk to be less with RALP compared to RRP[7] this study of a very large cohort of men operated by either retropubic or robot assisted laparoscopic prostatectomy will shed further light on this question.

The primary aim of this study is to assess the difference in risk of developing an inguinal hernia within 2 years of a prostatectomy comparing the techniques of RRP and RALP.

This statistical analysis plan was completed and finalized before the personnel involved in the project started the analyses of data.

## ANALYSIS OBJECTIVES

The primary objective is to compare the risk of developing an inguinal hernia after open RRP respectively RALP within 2 years.

The secondary objective is to evaluate potential risk factors for developing an inguinal hernia, after prostatectomy

## STUDY METHODS

We will use data from the entire cohort in the LAPPRO trial (n=3706). Baseline characteristic of patients and operation is retrieved through perioperative CRF and questionnaire. Information regarding postoperative formation of an inguinal hernia is retrieved through patient questionnaires 6-12 weeks, 12 months and 24 months after surgery as well as CRF answered by doctor at clinical follow-up 12 weeks, 12 months and 24 months after surgery.

Specific questions to be analysed are listed in the section of Variables and Endpoints.

## ANALYSIS POPULATION, TYPE OF ANALYSIS

### *Analysis population*

The entire cohort in the LAPPRO trial (n=3706), where RALP was compared with RRP. Since it is a non-randomized study patient will be analysed as-treated.

## VARIABLES AND ENDPOINTS

### *Primary objective*

The estimation of the incidence of hernia formation after prostatectomy is based on physician reports of surgery due to inguinal hernia and patient reports on seeking health care due to suspected inguinal hernia.

PRE/PERIOPERATIVE INDICATION OF GROIN HERNIA IS BASED UPON:

#### **Preoperative questionnaire**

If the patient has, or have had, an inguinal hernia (QoL1, Q41 and Q46).

#### **CRF perioperatively**

Item 18-23: Other, same time surgery,

PHYSICIAN REPORTS OF SURGERY DUE TO INGUINAL HERNIA ARE BASED ON:

#### **CRF perioperatively**

Item 18-23: Other, same time surgery,

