**Questionnaire 24 months**

Q 50: Have you contacted the health care due to groin hernia? (Yes/No)

Q 58: Have you contacted the health care due other reasons? (Yes/No). If yes - reason for contact.

Q 59-77: Have you been re-admitted to hospital? (Yes/No). If yes – reason for and date of re-admittance? Only applicable if date is after prostate surgery date.

Q 78-90: Have you had surgery after your prostate surgery during the past year? (Yes/No). If yes – reason and date.

If at least one of the CRF reports indicates the patient has been re-operated or at least one of the items in the questionnaire indicates a suspected hernia formation, then the outcome will be defined as the occurrence of hernia (positive outcome).

If neither the CRF nor the questionnaire reported events related to inguinal hernia formation, then the outcome will be defined as the no occurrence of hernia (negative outcome).

Missing values will be interpreted as absence of hernia

The primary endpoint is proportion of patients with at least one inguinal hernia within 24 months after surgery.

Possible preoperative risk factors for inguinal herniaThe following risk factors for developing an inguinal hernia will be evaluated:

1. Age
2. Physical workload

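### Surgery done during the prostatectomy is listed as a source for both pre-existing hernia and the postoperative hernia outcome, and the SAP does not settle which applies

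*SAP*

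**What the plan says.** The SAP's section VARIABLES AND ENDPOINTS, Primary objective, sets out two source lists one after the other.

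- The first opens with "PRE/PERIOPERATIVE INDICATION OF GROIN HERNIA IS BASED UPON". It names the preoperative questionnaire and then, under CRF perioperatively, "Item 18-23: Other, same time surgery".
- The second opens with "PHYSICIAN REPORTS OF SURGERY DUE TO INGUINAL HERNIA ARE BASED ON". Its first entry is the same perioperative CRF item in the same words. The 6-12 week, 12-month and 24-month CRFs follow, each with a date and NOMESCO JAB codes.

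The second list matters because of the sentence that opens the section: "The estimation of the incidence of hernia formation after prostatectomy is based on physician reports of surgery due to inguinal hernia", together with patient reports of seeking care.

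Items 18-23 appear a third time in the later block on baseline characteristics and risk factors, again under CRF perioperatively.

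The rules that classify a patient stand at the end of the subsection Questionnaire 24 months. The positive rule begins "If at least one of the CRF reports indicates the patient has been re-operated" and adds any questionnaire item that indicates a suspected hernia. The negative rule begins "If neither the CRF nor the questionnaire reported events related to inguinal hernia formation". The endpoint is then given as: "The primary endpoint is proportion of patients with at least one inguinal hernia within 24 months after surgery".

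**The concern.** A hernia repaired during the prostatectomy was there before the operation ended. It cannot have developed afterwards, so a record of that repair does not belong among the sources for a postoperative outcome.

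Two things are at stake.

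1. **The comparison of techniques.** This is a non-randomized, as-treated comparison of the whole cohort of 3706, with no exclusion for a hernia found at surgery. Counting same-session repairs as events adds cases that are not part of the question. Equal addition in both arms pulls the risk ratio toward 1. Unequal addition moves it in either direction.
2. **The risk-factor analysis.** Prior hernia is risk factor 7, and it is evaluated in the same model as the surgical method (Statistical method). If the same record feeds both prior hernia and the outcome, part of that association arises by construction.

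**Working it through.** **Step 1. What the rules do with one patient.** Take a man whose inguinal hernia was repaired during the prostatectomy, with no later hernia report from physician or patient.

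| SAP text | Class |
|---|---|
| Outcome source list (includes items 18-23) | positive |
| Positive rule (re-operated, or a questionnaire item) | not met: a same-session repair is not a re-operation |
| Endpoint (within 24 months after surgery) | not met |
| Negative rule (no hernia-related event in CRF or questionnaire) | not clearly met: a CRF did record a hernia repair |

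The texts disagree, and none of them mentions this patient. The limit to dates after the prostate surgery is attached only to the questionnaire re-admission items (Q46-54, Q48-66, Q59-77), so it does not settle the matter for a CRF item.

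**Step 2. The SAP's own figures.** Inputs from Sample size: 2764 RALP and 942 RRP; 6% vs 7.5% or 10% vs 12.5%; two-sided 5%. The stated power is about 35% and 55%. A two-proportion test with continuity correction gives 34.8% and 54.9%. The pooled test without correction gives 37.6% and 57.2%. The stated figures reproduce, and they do not depend on this point.

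**Step 3. Illustration of size.** The SAP gives no rate of concurrent repair, so every value of c below is an assumption. For an arm with true later incidence p and a share c repaired in the same session and counted as events:

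observed risk = p + (1 − p) × c

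This takes later hernia to be equally likely with and without a concurrent repair. With p = 0.10 (RALP) and 0.125 (RRP), the crude risk ratio (RR) without the item is 0.10 / 0.125 = 0.80.

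| c in RALP | c in RRP | Observed RALP | Observed RRP | Crude RR |
|---|---|---|---|---|
| 1% | 1% | 0.10 + 0.90 × 0.01 = 0.109 | 0.125 + 0.875 × 0.01 = 0.13375 | 0.815 |
| 5% | 5% | 0.10 + 0.90 × 0.05 = 0.145 | 0.125 + 0.875 × 0.05 = 0.16875 | 0.859 |
| 3% | 1% | 0.10 + 0.90 × 0.03 = 0.127 | 0.13375 | 0.95 |
| 1% | 3% | 0.109 | 0.125 + 0.875 × 0.03 = 0.15125 | 0.72 |

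At an equal 1%, the added events are 2764 × 0.90 × 0.01 ≈ 25 in RALP and 942 × 0.875 × 0.01 ≈ 8 in RRP. Power by the pooled test without correction falls from 57.2% to 53.6%. At an equal 5% it falls to 42.2%.

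**The case against.** The strongest reply is that the source list only says where to look, while the classification rule decides. That rule requires a re-operation, the endpoint lies after surgery, and the section's opening sentence concerns hernia formation after prostatectomy. On that reading no concurrent repair is ever counted, and the duplicate entry is a copying slip. Much of this stands: a reader might infer that hernias present at surgery will be counted as new, and the SAP does not establish that. It does not rule it out either, because the outcome list names the item and the negative rule leaves such a patient unplaced.

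Other stronger readings also go too far:

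- **All hernias present at surgery are affected.** Only those repaired in the same session can enter through this item.
- **Any concurrent procedure could count, since items 18-23 carry no JAB codes.** The heading over the list already limits it to surgery for inguinal hernia.
- **The record certainly sits on both sides of the model.** No sentence says that items 18-23 define risk factor 7. That factor concerns hernia or hernia surgery before prostatectomy, and the baseline section takes previous hernia surgery from questionnaire Q46 and Q47. The overlap is plausible from the first source list, but it is not stated.
- **The risk ratio could reverse.** From 6% vs 7.5%, with 3% concurrent repair in RALP and 1% in RRP, the crude ratio is (0.06 + 0.94 × 0.03) / (0.075 + 0.925 × 0.01) = 0.0882 / 0.08425 = 1.05. This needs a threefold difference between arms that nothing in the SAP supports.

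All these ratios are crude. The planned modified Poisson model has prior hernia among its candidate covariates. If that covariate includes concurrent repairs, adjustment could absorb some of the distortion, though not necessarily all.

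**Conclusion.** The point holds as an internal contradiction in the definition of the primary endpoint. The same record is a source for hernia present at surgery and for hernia arising after it, and the classification rules do not resolve the conflict. The duplicate listing is certain; whether the double count would occur in practice is not.

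The size of any bias is unknown. Under the assumptions shown, an equal 1% barely moves the crude risk ratio (0.80 to 0.815). Rates of 1% and 3% give 0.72 if RRP has the higher rate and 0.95 if RALP does. These figures show how sensitive the ratio is to a difference between arms; they do not predict one. The correction is still worth making, because the entry decides who is an event in the primary endpoint and removing it is cheap.

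**What to change.** 1. Delete items 18-23 of the perioperative CRF from the list of physician reports that define the outcome.
2. Keep the item only as a source for pre-existing hernia, limited to inguinal hernia repair. Do not make that limit depend on JAB codes unless the perioperative CRF records them; the SAP does not show that it does.
3. Add to the outcome rules at the end of Questionnaire 24 months that a repair done during the prostatectomy is not an outcome event, so that the positive and negative rules agree.
4. Apply the limit to dates after the prostate surgery to the dated CRF re-operation items and the dated questionnaire items on surgery and re-admission. Leave the contact items Q22, Q39 and Q50 as they are: they are yes/no items with no date listed, and a date requirement would remove them as a source.

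The cost is a few lines of SAP text and a small change to the derivation code. The downside is slightly fewer events if concurrent repairs would otherwise have been counted.

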#### **CRF 6-12 weeks**

Item 47-48: Has the patient been re-operated due to hernia? (Yes/No). Date and NOMESCO code JAB 10, 11, 20, 30, 40, 96, 97

Item 49-50: Has the patient been reoperated for other reason? (Yes/No). Date and NOMESCO code JAB 10, 11, 20, 30, 40, 96, 97

#### **CRF 12 months**

Item 38-40: Has the patient been re-operated due to inguinal hernia? (Yes/No). Date and NOMESCO code JAB 10, 11, 20, 30, 40, 96, 97

Item 41-49: Has the patient been reoperated for other reason? (Yes/No). Date and NOMESCO code JAB 10, 11, 20, 30, 40, 96, 97

#### **CRF 24 months**

Item 38-40: Has the patient been re-operated due to inguinal hernia? (Yes/No). Date and NOMESCO code JAB 10, 11, 20, 30, 40, 96, 97

Item 41-49: Has the patient been reoperated for other reason? (Yes/No). Date and NOMESCO code JAB 10, 11, 20, 30, 40, 96, 97

PATIENT REPORTS ON SEEKING HEALTH CARE DUE TO SUSPECTED INGUINAL HERNIA ARE BASED ON THE FOLLOWING:

**Questionnaire three months:**

Q 22: Have you contacted the health care due to groin hernia? (Yes/No)

Q 31: Have you contacted the health care due other reasons? (Yes/No). If yes - reason for contact.

Q 46-54: Have you been re-admitted to hospital? (Yes/No). If yes – reason for and date of re-admittance? Only applicable if date is after prostate surgery date.

**Questionnaire 12 months**

Q 39: Have you contacted the health care due to groin hernia? (Yes/No)

Q 47: Have you contacted the health care due other reasons? (Yes/No). If yes - reason for contact.

Q 48-66: Have you been re-admitted to hospital? (Yes/No). If yes – reason for and date of re-admittance? Only applicable if date is after prostate surgery date.

Q 67-79: Have you had surgery after your prostate surgery during the past year? (Yes/No). If yes – reason and date.

**Questionnaire 24 months**

Q 50: Have you contacted the health care due to groin hernia? (Yes/No)

Q 58: Have you contacted the health care due other reasons? (Yes/No). If yes - reason for contact.

Q 59-77: Have you been re-admitted to hospital? (Yes/No). If yes – reason for and date of re-admittance? Only applicable if date is after prostate surgery date.

Q 78-90: Have you had surgery after your prostate surgery during the past year? (Yes/No). If yes – reason and date.

If at least one of the CRF reports indicates the patient has been re-operated or at least one of the items in the questionnaire indicates a suspected hernia formation, then the outcome will be defined as the occurrence of hernia (positive outcome).

If neither the CRF nor the questionnaire reported events related to inguinal hernia formation, then the outcome will be defined as the no occurrence of hernia (negative outcome).

Missing values will be interpreted as absence of hernia

The primary endpoint is proportion of patients with at least one inguinal hernia within 24 months after surgery.

Possible preoperative risk factors for inguinal herniaThe following risk factors for developing an inguinal hernia will be evaluated:

1. Age
2. Physical workload

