### **CRF 24 months**

Item 51: Patient drop-out (Yes/No)

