## **HANDLING OF MISSING VALUES AND OTHER DATA CONVENTIONS**

In order to handle the issue with missing data of risk factors used in the model, multiple imputation by means of chained equations (MICE) will be used.

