#### **Statistical method**

The primary objective of evaluating the association between hernia incidence and operation and the evaluation of risk factor will be done simultaneously with the same statistical model. The relative risk of at least one inguinal hernia within 24 months after surgery, comparing surgical methods (RALP, RRP), will be modelled using a modified Poisson regression approach of Zou ([10]).

Except for the exposure, the surgical method (RALP, RRP), possible risk factors (age, physical workload, BMI, diabetes, pulmonary disease, smoking, hernia prior operation, physical activity and tumour size) will be evaluated by the same algorithm introduced by Bursac ("Purposeful selection of variables in logistic regression", Source Code for Biology and Medicine 2008;17). This model might also include interactions.

The key secondary objective will evaluate the same risk factors, but will include Lymph node dissection (yes/no) in the model.

The secondary objectives will be evaluated in an analogous way, using the risk factors ....

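### Scoring every missing outcome as no hernia understates 24-month incidence, and biases the RALP:RRP risk ratio if the share of hernias missed differs by technique

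*SAP*

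**What the plan says.** Under Variables and endpoints the outcome is positive if any CRF reports a re-operation or if "at least one of the items in the questionnaire indicates a suspected hernia formation". It is negative if neither source reported an event. The next sentence reads "Missing values will be interpreted as absence of hernia". The endpoint follows: "The primary endpoint is proportion of patients with at least one inguinal hernia within 24 months after surgery".

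Study methods lists the sources as "patient questionnaires 6-12 weeks, 12 months and 24 months after surgery", plus physician CRFs at 12 weeks, 12 months and 24 months. The CRFs supply re-operation. The questionnaires supply care-seeking, together with re-admission and, at 12 and 24 months, surgery.

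The section on missing values deals only with covariates: for "missing data of risk factors used in the model, multiple imputation by means of chained equations (MICE) will be used". Item 51 of each follow-up CRF records drop-out, but no definition or analysis uses it. The analysis population is the entire cohort of 3706, and the relative risk "will be modelled using a modified Poisson regression approach of Zou".

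**The concern.** The missing-value sentence does not separate two situations. A blank hernia item on a returned form can reasonably be read as no. An absent form, or a man who has left the study, carries no such information. Yet a man lost after the 6-12 week contact with nothing reported is analysed as if he had been observed hernia-free for 24 months.

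Two results are at stake. The endpoint proportion is too low in each group whenever some hernias go unreported. The comparison of techniques is distorted if the missed share differs between them. The trial is non-randomised and spans 14 departments, so equal capture cannot be taken for granted. The error lies in the outcome itself, so adjusting for the listed risk factors cannot be relied on to remove it. The SAP plans no censoring, minimum follow-up, outcome sensitivity analysis or table of completeness by technique that would reveal the problem.

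**Working it through.** **Inputs from the SAP (Sample size).** 2764 RALP and 942 RRP patients, 3706 in total; two-sided 5% test; 6% vs 7.5% with about 35% power; 10% vs 12.5% with 55% power. Missing-outcome rates are not given, so every value of m below is an assumption.

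**Reproducing the stated power.** For two proportions a (RALP) and b (RRP), let s0 be the pooled standard error, s1 the unpooled one, and d = |a − b|. Power is Φ((d − 1.96·s0)/s1), plus the small opposite tail.
- 10% vs 12.5%: s0 = 0.01163 and s1 = 0.01219, so Φ((0.025 − 0.02280)/0.01219) = Φ(0.18) = 57.2%. Subtracting the continuity correction 0.5(1/2764 + 1/942) = 0.00071 from d gives 54.9%.
- 6% vs 7.5%: 37.6% uncorrected, 34.8% corrected.

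The corrected version matches both stated figures. The uncorrected version is used below, so the no-loss reference is 57%. It is an unadjusted approximation to the planned model.

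**Effect of the rule.** If a share m of an arm's true hernias is reported by no source and scored no, the observed risk is p(1 − m). Hence observed RR = true RR × (1 − m_RALP)/(1 − m_RRP).

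True risks 10% and 12.5%, true RR 0.80:

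| m RALP / RRP | Observed risks | Observed RR | Power |
|---|---|---|---|
| 0 / 0 | 10.0% / 12.5% | 0.80 | 57% |
| 5% / 10% | 9.5% / 11.25% | 0.84 | 35% |
| 10% / 5% | 9.0% / 11.9% | 0.76 | 72% |
| 10% / 20% | 9.0% / 10.0% | 0.90 | 16% |
| 20% / 10% | 8.0% / 11.25% | 0.71 | 84% |
| 15% / 15% | 8.5% / 10.6% | 0.80 | 50% |

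The 10%/20% row in full: s0 = 0.01093 and s1 = 0.01119, so Φ((0.010 − 0.02143)/0.01119) = Φ(−1.02) = 15.4%, and 15.6% with the opposite tail. In the 20%/10% and 10%/5% rows the higher power comes from an exaggerated difference and is no gain.

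For comparison, if the same percentages of men were lost at random and only the others analysed, RR would stay at 0.80. Power would be 54% for 5%/10% and 50% for 10%/20%.

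**No true difference.** With 11.2% in both groups (assumed, about midway between 10% and 12.5%), m of 10%/20% gives 10.1% vs 9.0%, RR 1.125, and rejection in about 16% of trials instead of 5%. With m of 5%/10%, rejection is about 7%.

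**Drop-out is not m.** Suppose 10% of RALP and 20% of RRP men are lost, but half of their hernias were reported earlier (assumption). Then m is 5%/10%, so RR is 0.84 and not 0.90.

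**Equal loss need not be harmless.** Suppose 20% are lost in each arm and the lost RALP men have twice the risk of those followed. RALP risk among those followed is 0.10/(0.8 + 0.2 × 2) = 0.0833, and the observed risk is 0.8 × 0.0833 = 0.0667. For RRP it is 0.8 × 0.125 = 0.10. The observed RR is 0.667.

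**The case against.** The strongest defence is that the outcome has many chances to be captured. One positive item in any of three questionnaires or three follow-up CRFs is enough, so the missed share may be well below the drop-out rate. This stands, and it makes scenarios that equate the two an upper bound when loss is unrelated to hernia risk.

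The SAP also gives no loss rate, overall or by technique. It calls the 3706 evaluable, against 4003 included, so 297 men were removed beforehand. Whether non-responders were among them cannot be told. Loss within the 3706 may be small. This also stands.

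Under equal loss unrelated to hernia risk the risk ratio is unchanged. The fall in power (57% to 50% at 15%) is almost all due to the loss itself, since analysing only those observed gives 51%. In that case the harm is confined to understated incidence. The study was, moreover, not sized for hernia.

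Two stronger readings are tempting and not supported. A reader might infer that the risk ratio is biased whenever loss to follow-up differs. What matters is the share of hernias missed: unequal loss can be offset by different risk among those lost, and equal loss can still bias. A reader might also infer that the false negatives corrupt the imputation of risk factors. The SAP does not list the variables in that imputation model, so this cannot be shown.

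None of this limits the rule to blank items or provides a test of it.

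**Conclusion.** The point holds. As written, the rule turns absent information into observed freedom from hernia. It understates the 24-month proportion in any group where hernias are missed, and it biases the risk ratio when the missed share differs by technique.

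The bias can go either way and its size cannot be established from the SAP. At the SAP's own 10% and 12.5%, a five-point difference in the missed share moves 0.80 to 0.84 or 0.76, and a ten-point difference moves it to 0.90 or 0.71. These figures rest on assumed missed shares and an unadjusted two-proportion calculation. They show how sensitive the result is and do not predict it. A reader might take the 16% power or 16% false-positive figure as expected performance; the document gives no basis for that.

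The rule should be corrected before analysis, since the remedy uses forms already collected. Because the loss is unknown, it cannot be said that the rule by itself invalidates the comparison.

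**What to change.** Replace the missing-value sentence, and the preceding rule that scores no reported event as negative, with the following:

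1. A blank hernia item on a returned form counts as no.
2. A hernia reported at any wave counts as an event, whatever is missing later.
3. A missing follow-up form leaves that wave's component missing, not negative: re-operation for the CRF, care-seeking for the questionnaire. A 24-month CRF alone does not settle care-seeking. A 24-month questionnaire does not fully replace a missed 12-month one, since its surgery item covers only the past year.
4. For men without an event, impute the missing wave-level outcomes within MICE, conditional on technique, covariates and being event-free at earlier completed waves. Then derive the 24-month outcome for the modified Poisson model.
5. Keep missing means no hernia as a sensitivity analysis, and report form completeness by technique.

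The conditioning in step 4 is essential. Take 10%/20% loss with half of the lost men's hernias reported earlier. Keeping those events and simply omitting the remaining lost men gives 0.095/0.905 = 10.5% and 0.1125/0.8125 = 13.8%. The RR is then 0.76, an error about as large as the present rule's 0.84, in the other direction. Censoring at the last form is not a ready alternative: the planned model is for a binary outcome, and the SAP lists no date for the direct care-contact questions.

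The cost is revised SAP wording, modest programming and slightly wider confidence intervals. No new data are needed.
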